### Statistical analysis

3.4

Initial data inspection will include descriptive statistics to summarize demographic and clinical characteristics and to identify potential outliers. Outliers will be evaluated according to standard practices, including visual inspection of boxplots and standardized residuals (values exceeding ±3 standard deviations), and decisions on their treatment (e.g., retention, transformation, or exclusion) will be justified and documented.

The distribution of each variable will be assessed using both visual (histograms, Q-Q plots) and statistical methods (Shapiro-Wilk test) to guide the choice of parametric or non-parametric analyses. For the main analyses, a two-way repeated-measures ANOVA will be conducted with Group (three levels: two robot-assisted interventions and one active control) and Time (three levels: T0, T1, T2) as factors. Post-hoc comparisons will be performed with appropriate correction for multiple testing.

Additionally, correlation analyses and regression models (both linear and logistic, where appropriate) will be conducted to explore associations between clinical outcomes, caregiver measures, and device-derived metrics, as well as potential predictive factors. All analyses will be conducted using (version 4.1.2; R Core Team, 2021) and Matlab (The Math Works, Inc., 2025) and/or equivalent statistical software, and significance thresholds will be set *a priori*.

Results will be reported as aggregated data to ensure participant anonymity.

Clinical data will be analyzed at the Department of Biomedical, Metabolic, and Neuroscience of the University of Modena and Reggio Emilia.

Device- and sensor-derived data, including kinematic and interaction metrics from robot-assisted interventions, will be analyzed in relation to clinical and behavioral outcomes by experts at the University of Genoa and the University of Florence.

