### Sample size calculation

3.5

To the best of our knowledge, robust evidence on the effect size of robot-mediated interventions primarily aimed at usability and behavioral outcomes in individuals with neurocognitive disorders is currently lacking. Therefore, a formal sample size calculation based on statistical power is not feasible. The proposed sample size is determined according to a pragmatic approach, taking into account the epidemiology of apathy within the target population and previous studies in the field of robotic interventions and dementia, which typically include small sample sizes (often fewer than 20 patients per arm; Hung et al., 2021; Mancioppi et al., 2019; Moyle et al., 2019).

In line with these considerations, the study aims to enroll approximately 25 patients per arm who will complete the trial. Accounting for an expected attrition rate of approximately 6%, the total sample to be randomized was set at 80 patients, allocated with a 1:1:1 ratio directly at enrollment (exact allocation per arm may vary slightly depending on block randomization, approximately 27, 27, and 26 patients per arm, given block randomization). The primary analysis will be conducted on an intention-to-treat basis, including all randomized participants; a per-protocol analysis restricted to patients who complete the trial will be reported as a secondary analysis.

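### Distribution checks on each variable may switch the main comparison between parametric and non-parametric tests, because nothing exempts the named Group × Time ANOVA

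*Protocol article*

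**What the plan says.** Two adjacent sentences in section 3.4 (Statistical analysis) matter here.

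- The first has every variable inspected with histograms, Q-Q plots and "statistical methods (Shapiro-Wilk test) to guide the choice of parametric or non-parametric analyses".
- The second reads "For the main analyses, a two-way repeated-measures ANOVA will be conducted with Group (three levels: two robot-assisted interventions and one active control" and adds Time (T0, T1, T2) as the other factor.

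The article does not say whether the first sentence governs the second. It names no non-parametric method, and it does not say whether the check is made on all patients together, at each visit, or in each arm at each visit. On alpha it says only that "significance thresholds will be set" in advance, without a value.

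Section 3.1 (Primary outcome measures) lists four instruments under clinical improvement of apathy (AES, Yoni-48, ESCoT, IAPS), followed by robot-interaction and kinematic measures. Section 2.4 (Randomization and blinding) keeps the data analysts blinded to allocation.

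**The concern.** A main test chosen after looking at the outcome data is not fixed in advance. If the choice is made variable by variable, the primary endpoints of one trial can end up with different tests.

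Two features make this worse. First, the ANOVA's distributional assumption concerns its residuals, whereas the check is placed on the variables. Second, a move to a rank test can change the question as well as the method, because some familiar rank tests do not address Group × Time. That matters here: section 4.1 (Anticipated results) expects the robot arms to improve from baseline about as much as occupational therapy does. In that situation a test within each arm tends to be positive and says nothing about the comparison with control.

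**Working it through.** **Inputs from the article.** Three arms, three visits, 1:1:1 allocation of 80 patients (about 27/27/26), about 25 completers per arm, about 6% attrition. **Assumed, because the article gives none:** alpha 0.05 for Shapiro-Wilk and for the trial test, between-visit correlation, skewness and effect size. Simulations used 1,500 trials per setting, so the Monte Carlo standard error is about 0.6 points near 5% (√(0.05 × 0.95/1,500)) and 1.2 points near 70% (√(0.7 × 0.3/1,500)).

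**1. The plan's own figure.** Section 3.5 (Sample size calculation) says "the study aims to enroll approximately 25 patients per arm who will complete the trial" and "Accounting for an expected attrition rate of approximately 6%, the total sample to be randomized was set at 80 patients". 3 × 25 = 75, and 75/0.94 = 79.8, which rounds up to 80. The figure reproduces, and this point does not change it.

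**2. Exactly normal data.** Suppose any rejection triggers a switch. With k independent checks the chance of a false trigger is 1 − 0.95^k. The simulations used correlations of 0.5 and 0.7 between visits.

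| Unit checked | k | Formula | Simulated |
|---|---|---|---|
| One variable, all 80 patients | 1 | 5.0% | 4.5–5.5% |
| Any of three visits | 3 | 14.3% | 13.7–14.5% |
| Any of nine arm-by-visit cells | 9 | 37.0% | 35.6–37.3% |

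**3. Mildly skewed data.** Two shapes were tried: gamma with shape 8 (skewness 2/√8 = 0.71) and lognormal with sigma 0.25 (skewness (e^0.0625 + 2) × √(e^0.0625 − 1) = 0.78).

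- One test on 80 patients rejects in 58–64%.
- One test on 27 patients rejects in 22–25%.
- At least one of three visits fails in 89–93%.
- At least one of nine cells fails in 86–90%.

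**4. Variable or residual.** Errors were normal and two of the three arms were shifted. Shapiro-Wilk was applied to the pooled variable and to the residuals from arm means.

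| Shift | Variable rejected | Residuals rejected |
|---|---|---|
| 1 SD | 4.8% | 4.9% |
| 1.5 SD | 6.0% | 4.2% |
| 2 SD | 14.7% | 4.3% |

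The distinction matters only for very large group differences. It disappears if each cell is checked separately, since a cell's values and their deviations from the cell mean differ by a constant.

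**5. What a switch could do.** Normal data, correlation 0.6, percentage of trials significant at 0.05:

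| Scenario | Group × Time F | Kruskal-Wallis at T1 | Kruskal-Wallis on T1 − T0 | Friedman, at least one arm |
|---|---|---|---|---|
| All arms change by 0.5 SD, no interaction | 5.6 | 4.5 | 5.6 | 98.0 |
| Same, plus a 0.6 SD shift of both robot arms at every visit | 5.6 | 57.8 | 4.8 | 96.1 |
| Interaction: both robot arms shift 0.6 SD at T1 and T2 | 72.7 | 58.2 | 66.7 | 97.8 |

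Friedman responds to change over time in any arm. Kruskal-Wallis at T1 ignores baseline: it picks up a difference already present at T0 and loses power when there is a true interaction. The rank test on change holds its level and loses 72.7 − 66.7 = 6.0 points of power.

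**The case against.** The strongest reply is that the ANOVA sentence carries no condition. On that reading the main test is fixed, and the distribution check serves the correlations, descriptive summaries and device metrics. This is possible, but the check covers every variable and comes directly before the main analysis with no exemption, so the text does not secure that reading.

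A reader might infer more: that Shapiro-Wilk alone decides, that chance therefore picks the main test, and that the fallback will not test Group × Time. The article does not support this. It says the checks guide the choice, and plots are used as well. It states no any-rejection rule, so the 14% and 37% figures show what such a rule would do, not what the plan prescribes. A rejection of truly skewed data is a correct detection, not chance. Neither Kruskal-Wallis nor Friedman is named, and a rank test on change from baseline keeps the T0–T1 comparison at modest cost. The second scenario in step 5 also needs a group difference present at baseline, which randomization leaves to chance imbalance.

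Two further replies stand in part. Analyst blinding makes it hard to steer the choice towards an arm, although it does not make the test pre-specified. And the trigger, the unit and the alternative may be set out in a statistical analysis plan that is not shown. Their absence is not the point; the point is that the article itself ties the choice of analysis to the data.

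**Conclusion.** The point holds in a limited form. Read together, the two sentences allow the main test to depend on the data and to differ between endpoints. How often that would happen cannot be known from the article. Under an assumed strict 0.05 rule it ranges from about 5% to 37% for exactly normal data, according to the unit checked, and is about 60% for one test on 80 patients with skewness of about 0.7.

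The harm from a switch depends on the fallback. It is small for a rank test on change from baseline, and it is a change of question for Kruskal-Wallis at a single visit or Friedman within an arm. The power figures come from one assumed setting (0.6 SD effect, correlation 0.6) and are illustrative. The variable-versus-residual issue is real but minor. It does not follow that the planned comparison will be abandoned or decided by chance. The passage should be tightened because doing so is cheap and the main comparison should not be left open.

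**What to change.** Add to section 3.4 that:

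- the between-group, baseline-using Group × Time contrast is the main analysis of the AES and the other clinical scales, whatever the Shapiro-Wilk result;
- distribution is judged on the residuals of that model;
- if residuals are clearly skewed, the same contrast is kept and reported with bootstrap or robust confidence intervals;
- a rank-based analysis of that contrast, for example rank ANCOVA or a rank test on change from baseline, is reported as a sensitivity analysis.

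The distribution checks can stay for descriptive, correlation and device-metric analyses, where they are sensible. The change takes a few sentences and slightly more analysis work. It needs no new data and leaves the total at 80.

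### The repeated-measures ANOVA named as the main analysis, in its standard form without imputation, cannot include all randomised patients, and leaves nearly the same set as the per-protocol analysis

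*Protocol article*

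**What the plan says.** Section 3.4 (Statistical analysis) fixes the method for the main analyses: "a two-way repeated-measures ANOVA will be conducted with Group (three levels: two robot-assisted interventions and one active control) and Time" as the second factor, specified as "Time (three levels: T0, T1, T2) as factors". The regression models in the same section are for exploring associations and predictors. They are not a second route to the treatment comparison.

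Section 3.5 (Sample size calculation) fixes the populations. On the primary analysis: "The primary analysis will be conducted on an intention-to-treat basis, including all randomized participants". On the secondary one: "a per-protocol analysis restricted to patients who complete the trial will be reported as a secondary analysis". It also says that "the study aims to enroll approximately 25 patients per arm who will complete the trial", and reaches 80 randomised patients by allowing for attrition: "Accounting for an expected attrition rate of approximately 6" per cent.

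Section 3.4 also flags values beyond 3 standard deviations for evaluation and says that "decisions on their treatment (e.g., retention, transformation, or exclusion) will be justified and documented".

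Section 5 (Limitations) acknowledges drop-out, but the measures it offers are training, technical support and checking of equipment. None is an analysis method.

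**The concern.** The article fixes both the analysis population and the model, and the two do not fit together as written. A classical Group x Time repeated-measures ANOVA works on complete triplets of T0, T1 and T2. A patient who attends T0 and T1 but misses T2 contributes nothing in the standard form, although two of the three values were observed. The headline result would then be labelled intention-to-treat but rest on patients with complete data.

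The secondary analysis would not expose the problem. It is restricted to patients who complete the trial, which is close to what the ANOVA does anyway. Agreement between the two would look like robustness but would mostly reflect the use of the same patients.

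If loss to follow-up is related to outcome and differs between arms, the completer comparison is biased. Device and connectivity faults, which Section 5 lists as a limitation, can arise only where a robot is installed, so arm-related loss is plausible here. That is an inference; the article does not state it.

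**Working it through.** **Inputs.** From Section 3.5: target of about 25 completers per arm (75 in total), attrition about 6%, 80 randomised, arms of about 27, 27 and 26. From Section 3.4: three visits in the model. The size of any outcome deficit in lost patients is not in the article; 0.5 to 1.5 SD is an assumption. Attrition rates above 6% are also assumptions.

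**1. The plan's own figure.** 75 / (1 - 0.06) = 79.8, rounded up to 80. It reproduces.

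**2. Patients left in the ANOVA.** 80 x (1 - 0.06) = 75.2, so about 75 remain and about 5 are lost. This equals the number of completers that the plan aims for.

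| Attrition | Complete cases of 80 |
|---|---|
| 6% (plan) | about 75 |
| 10% (assumed) | 72 |
| 15% (assumed) | 68 |
| 20% (assumed) | 64 |

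**3. Does the software really drop them?** With simulated data in R (80 patients, three visits, T2 missing for 5), the multivariate form of the ANOVA used 75 patients. The error-strata form kept the incomplete rows but warned of a singular model, and part of the Time and Group x Time effects moved into the between-patient stratum. It keeps the patients at the price of a clean test.

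**4. Possible shift, worst case.** If a fraction f of an arm is lost and those patients would have scored d SD worse than those who stay, the arm's completer mean differs from its full mean by f x d. With all 5 losses in one 27-patient arm, f = 5/27 = 0.185:
- d = 0.5: 0.09 SD
- d = 1.0: 0.19 SD
- d = 1.5: 0.28 SD

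If drop-out risk were equal across arms, the chance that all 5 losses fall in one arm is (2 x C(27,5) + C(26,5)) / C(80,5) = 227,240 / 24,040,016, about 0.9%.

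**5. Possible shift, even spread.** With losses of 2/27, 2/27 and 1/26, the largest between-arm difference in f is 0.0741 - 0.0385 = 0.0356. Times 0.5 to 1.5 SD, this gives about 0.02 to 0.05 SD.

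**6. An intermediate scenario.** A simulation compared two arms of 27 with no true effect and assumed visit correlations of 0.5 to 0.6. Loss before T2 was at random in one arm and concentrated among patients with worse T1 scores in the other. The complete-case estimate of the between-arm difference in T0-to-T1 change was off by about 0.05 SD at 6% loss, 0.07 SD at 15% and 0.10 SD at 25%. Using everyone with T0 and T1 brought the error to about zero.

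**7. Extreme values.** 80 patients x 3 visits = 240 values per endpoint. Under normality, 240 x 0.0027 = 0.65 valid values would lie beyond 3 SD by chance. That is the expected number flagged, not the number deleted. If a flagged value were excluded, the standard ANOVA would lose the whole patient.

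**The case against.** The strongest reply is that the conflict rests partly on silence. The article states no complete-case rule, and missing-data handling is commonly left to an analysis plan, which is not shown. Imputation there would let the ANOVA run on all 80. This stands as a condition: the loss applies to the ANOVA as named, in its standard form and without imputation. It does not remove the point, because the article itself commits to both the model and the population, and a better-suited model is readily available.

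A reader might infer four stronger things that the article does not support.

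- *That the primary and per-protocol sets are identical.* Trial completion is not defined as having all three visits observed. A patient who stops the intervention but attends T1 and T2 would be in the ANOVA and perhaps not in the per-protocol set. One who misses T1 but attends T2 could be the reverse. The sets are nearly the same, not provably the same.
- *That the article names apathy, technical failure and severity as causes of drop-out that differ by arm.* Section 5 lists drop-out beside digital literacy, technical issues and severity, and links severity to adherence. It does not name apathy as a cause of drop-out or say that causes differ by arm. Section 2.4 stratifies randomisation by diagnosis, MoCA and apathy severity.
- *That the completer result is therefore biased, by up to 0.28 SD.* That figure needs every loss in one arm and an assumed deficit of 1.5 SD.
- *That the 3 SD rule removes patients.* It flags values for a documented decision, retention is among the options, and Section 2.4 keeps analysts blinded.

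**Conclusion.** The point holds in limited form. As written, the main analysis cannot deliver the stated intention-to-treat population unless missing visits are imputed, and the article mentions no such step. At the planned 6% attrition the ANOVA uses about 75 of 80 patients, nearly the per-protocol set, so the secondary analysis gives little check on the primary one.

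The likely effect on the estimate at 6% attrition is small: about 0.02 to 0.05 SD between arms if losses are spread evenly and lost patients would have done 0.5 to 1.5 SD worse. The 0.09 to 0.28 SD range is a worst case for a single arm. The problem grows if attrition exceeds 6% or is concentrated in one arm. Bias is a risk that the stated method leaves unprotected, not an established result.

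**What to change.** In Section 3.4, replace the ANOVA with a likelihood-based mixed model for repeated measures: fixed effects for arm, visit and arm-by-visit, unstructured within-patient covariance, patients analysed as randomised. Keep T0 in the outcome vector, so that every randomised patient with any assessment contributes. Section 2.2.2 places randomisation after the baseline assessment, so this should cover all 80, although a patient with T0 alone adds little to the arm comparison. A model of T1 and T2 only would still omit patients lost before T1. Multiple imputation is an acceptable alternative.

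Add one missing-not-at-random sensitivity analysis, for example delta-adjusted imputation. Keep valid extreme values in the primary analysis and show any exclusion only as a sensitivity analysis.

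In Section 3.5, define the per-protocol set by intervention received rather than by completing the trial, so that it answers a different question from the primary analysis.

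The cost is rewording in two sections and a few lines of R, with no new data. The small downside is reliance on a missing-at-random assumption, which the sensitivity analysis addresses.

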#### Assessment

2.2.1

At baseline (T0), post-intervention (T1, 6 weeks after T0), and follow-up assessment (T2, 5 weeks after T1), patients and their study partners will complete a comprehensive set of clinical, cognitive, behavioral, and psychosocial assessments, including:Neuropsychiatric Inventory (NPI; Cummings et al., 1994; Italian version by Binetti et al., 1998): assessment of non-cognitive behavioral disturbances in dementia across multiple domains, including frequency, severity, and caregiver distress.Apathy Evaluation Scale (AES; Marin et al., 1991; Italian version by Borgi et al., 2016): measurement of apathy in behavioral, cognitive, and emotional domains.Yoni-48 Task (Italian version by Isernia et al., 2022b; Isernia et al., 2023): computerized evaluation of first- and second-order affective and cognitive Theory of Mind (ToM).Edinburgh Social Cognition Test (ESCoT; Italian version by Isernia et al., 2022a): assessment of cognitive and affective ToM and understanding of interpersonal and intrapersonal social norms.International Affective Picture System (IAPS; Lang et al., 1997) with Self-Assessment Manikin (SAM; Bradley and Lang, 1994): evaluation of emotional valence and physiological arousal.Zarit Burden Inventory (Zarit et al., 1980; Italian version by Chattat et al., 2011): caregiver burden assessment.Quality of Life in Alzheimer’s Disease (QoL-AD; Logsdon et al., 1999; Italian version by Bianchetti et al., 2017): multidimensional quality-of-life assessment combining patient and caregiver ratings.Cognitive Reserve Index Questionnaire (CRIq; Italian version by Nucci et al., 2012): evaluation of cognitive reserve across education, occupational, and leisure activities.Cognitive assessments, including the Montreal Cognitive Assessment (MoCA; Nasreddine et al., 2005; Italian version by Santangelo et al., 2015).

The usability and the perceived usefulness, ease of use, and overall acceptance of the robotic systems will be subjectively evaluated at T1 using the System Usability Scale (SUS) and the Technology Acceptance Model (TAM).

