### Trial design

2.3

The study is designed as a single-blind, randomized controlled trial (RCT). Patients with neurocognitive disorders (both minor - i.e., MCI - and major, i.e., dementia), and presenting either MBI or BPSD, will be recruited from the Complex Units of Neurology and Geriatrics of the Azienda Ospedaliero-Universitaria di Modena (Modena), as well as from the Neurorehabilitation Units of the IRCCS Fondazione Don Carlo Gnocchi (Milan). After recruitment, individuals will be randomly assigned to one of two experimental groups involving robotic interventions (i.e., Telepresence robot or Pepper Robot) or to the active control group. Both the robotic and occupational therapy interventions will be conducted over 6 weeks. Primary and secondary outcome measures will be collected at baseline (T0), immediately post-intervention (T1, 6 weeks), and at follow-up (T2, 5 weeks after the end of the intervention, i.e., 11 weeks total time). The trial work plan is illustrated in Figure 1.

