### Randomization and blinding

2.4

Eligible patients will be randomized using the “blockrand” package in (version 4.1.2; R Core Team, 2021). Randomization will be performed separately for each recruitment center and, within each center, will be stratified according to clinical and demographics variables, including diagnosis, sex, age, years of education, MOntreal Cognitive Assessment (MOCA) score, and apathy severity as measured by the Neuropsychiatric Inventory (NPI) apathy subscale. The allocation sequence will be prepared by a researcher not involved in either treatment delivery or outcome assessments. Investigators responsible for treatment administration and evaluations will not have access to the randomization list. Once generated, the list will be uploaded to REDCap in a non-visible format. Upon the creation of each new patient record and study ID, REDCap will automatically assign patients to their study group according to the predefined allocation sequence. In addition, different user access levels within REDCap will ensure that group allocation remains concealed from outcome assessors.

Patients will be randomly assigned to one of the two experimental groups or to the active control group (1:1:1 ratio).

Given the nature of the interventions, blinding will not be feasible for recruiting clinicians, researchers administering the interventions, or patients. However, outcome assessments at baseline (T0), post-intervention (T1), and follow-up (T2), including clinical endpoints and clinical/psychological questionnaires, will be conducted by trained evaluators who are blinded to group allocation. In addition, data analysts will remain blinded to treatment assignment throughout the analysis phase.

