## Limitations

5

This study presents some intrinsic limitations, due to the implementation of innovative home-based robotic interventions. A first limitation concerns the unequal and non-standardized contact time across study arms. The occupational therapy control group follows the frequency defined by national care standards (Ministero della Salute, DPCM, 2017), the telerobot arm follows a fixed schedule of three 45-min sessions per week, while the Pepper robot arm allows for flexible, self-paced interactions with no upper limit. This design choice reflects the practical and technical characteristics of each modality rather than an attempt to equalize contact time, and it does not allow a complete separation between intervention-specific effects and non-specific effects related to attention and social contact, particularly in the comparison between the robotic arms and the active control group. Actual contact time in each arm will be recorded and may be used as a covariate in sensitivity analyses.

Furthermore, potential limitations include participant drop-out, variability in digital literacy among patients and caregivers, technical issues related to internet connectivity or device functioning, and differences in disease severity that could influence adherence to the intervention. To minimize these issues, all participants and caregivers will receive standardized training before the intervention, technical support will be available throughout the study, and the occupational therapist responsible for device installation will verify the correct functioning of the equipment. In addition, the pragmatic design of the trial and the relatively limited sample size should be considered when interpreting the findings. Nevertheless, the randomized controlled design and the inclusion of an active control group are expected to provide robust preliminary evidence regarding the feasibility, acceptability, and potential clinical effectiveness of robot-assisted interventions for apathy.

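### The planned Group × Time repeated-measures ANOVA rests on one common within-patient error; if the robot-versus-occupational-therapy contrasts use it, their standard errors can be wrong in either direction

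*Protocol article*

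**What the plan says.** Section 3.4 (Statistical analysis) of the protocol article names the main analysis: "a two-way repeated-measures ANOVA will be conducted with Group" at three levels and "Time (three levels: T0, T1, T2) as factors". On follow-up contrasts it says only that "Post-hoc comparisons will be performed with appropriate correction for multiple testing". It does not mention sphericity, a covariance structure or the error term for the contrasts. It does provide for checks of distributions and a possible move to non-parametric methods.

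The visits are set in section 2.2.1 (Assessment), "post-intervention (T1, 6 weeks after T0), and follow-up assessment (T2, 5 weeks after T1"), and confirmed in section 2.3 (Trial design), "5 weeks after the end of the intervention, i.e., 11 weeks total time". The visits therefore fall at weeks 0, 6 and 11; the first interval is on treatment and the second off it.

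Exposure follows a set programme in the tele-operated and occupational therapy arms. In the Pepper arm, section 5 (Limitations) describes "flexible, self-paced interactions with no upper limit".

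**The concern.** The primary objective is each robot arm against occupational therapy, so the comparisons that matter are between-arm contrasts in change from baseline at T1 and T2. A classical repeated-measures ANOVA averages the variability of all three visit differences over all three arms into one mean square. If those variances differ, the average is too small for the more variable contrasts and too large for the others.

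This design gives two reasons to doubt equality. T0 to T1 spans treatment and T1 to T2 does not, so the three visit pairs need not be equally correlated. Patients in the Pepper arm choose their own dose of contact, so their change may be more variable.

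A contrast whose standard error is too small has an interval that is too narrow and a false-positive rate above nominal. One whose standard error is too large loses power, which a trial with about 25 completers per arm can ill afford. A multiplicity correction repairs neither, because it works on p-values that are already wrong. A Greenhouse-Geisser type correction adjusts the overall F test and leaves pooled contrasts unchanged.

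**Working it through.** **Inputs from the article.** Three arms allocated 1:1:1, visits at weeks 0, 6 and 11, about 25 completers per arm, about 6% attrition. The only computed figure reproduces: 75 / 0.94 = 79.8, rounded up to 80. The article states no standard error, SD, correlation or power.

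**Assumptions.** Two-sided 5% per contrast before multiplicity correction, no true effect, normal data, equal visit SDs, and the correlations shown below.

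**Formulas, equal arms, unit SD.**
- The true variance of a change from T0 to Tj is 2(1 − r0j).
- The pooled error implies 2(1 − r̄) for every pair, where r̄ is the mean of the three correlations.
- Pooled SE / true SE = √[(1 − r̄)/(1 − r0j)]. Below 1 means that the SE is too small.
- Error degrees of freedom: pooled 2 × (75 − 3) = 144; contrast-specific, two arms, 2 × 25 − 2 = 48.

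**Worked example, T1-T2 correlation highest (0.5 / 0.45 / 0.8 for T0-T1 / T0-T2 / T1-T2).** r̄ = 1.75/3 = 0.583. T1-T0: √(0.417/0.50) = 0.91. T2-T0: √(0.417/0.55) = 0.87. Both are too small.

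**Worked example, correlation decaying with time (0.7 at six weeks).** T1-T2 is 0.7^(5/6) = 0.743 and T0-T2 is 0.7^(11/6) = 0.520, so r̄ = 0.654. T1-T0: √(0.346/0.30) = 1.07, too large. T2-T0: √(0.346/0.48) = 0.85, too small.

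**Rejection rates with the pooled error** (20,000 simulated trials per scenario, 25 per arm, equal arms):

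| Correlations T0-T1 / T0-T2 / T1-T2 | SE ratio T1-T0 | SE ratio T2-T0 | Rejects T1-T0 | Rejects T2-T0 |
|---|---|---|---|---|
| 0.5 / 0.5 / 0.5 | 1.00 | 1.00 | 5.1% | 4.9% |
| 0.5 / 0.45 / 0.7 | 0.95 | 0.90 | 6.6% | 7.9% |
| 0.5 / 0.45 / 0.8 | 0.91 | 0.87 | 7.3% | 8.7% |
| 0.6 / 0.5 / 0.85 | 0.94 | 0.84 | 6.8% | 10.2% |
| 0.7 / 0.52 / 0.743 (decay) | 1.07 | 0.85 | 3.6% | 9.3% |

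With the planned 27/27/26 per arm and six-week correlations from 0.5 to 0.9 under decay, the ranges are 3.3-4.0% at T1-T0 and 8.2-10.8% at T2-T0.

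**More variable Pepper arm** (correlations 0.5 / 0.45 / 0.8, Pepper SD 1.4 times the others). The mean arm variance factor is (1 + 1 + 1.96)/3 = 1.32.
- Pepper versus control, where 2.96 = 1.96 + 1: T1-T0 ratio √[(2 × 1.32 × 0.417)/(2.96 × 0.50)] = 0.86; T2-T0, with 0.55 in place of 0.50, 0.82. Rejection is about 9% and 10.5-10.8%.
- Tele-robot versus control: T1-T0 ratio √[(2 × 1.32 × 0.417)/(2 × 0.50)] = 1.05; T2-T0 1.00. Rejection is 4.1% and 5.1%.

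**Transient response.** If patients respond differently at T1 and none of that response persists to T2, T1-T0 is anticonservative and T2-T0 rejects only about 1%.

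**Alternative.** Contrast-specific unequal-variance errors stay within about half a percentage point of 5% in all scenarios in the table and in the Pepper scenario.

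**The case against.** The strongest case against the point has three parts.

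First, the article does not say that the contrasts use the pooled error. Contrast-specific errors, a multivariate test or a sphericity correction would all be compatible with its text, and such detail is commonly left to an SAP, which is not shown. This stands, and it makes the point conditional. What remains is that the article does name a model, and that model in its classical form carries the assumption.

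Second, the direction is not fixed. A reader might infer that the standard errors are simply too small for both robot contrasts at both visits. The documents do not support that. With correlation decaying over the trial's own spacing, the T1-T0 contrast is conservative. With a more variable Pepper arm, the tele-robot contrast is not inflated. Both visits come out too small only under particular patterns, such as a T1-T2 correlation above both baseline correlations.

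Third, a reader might infer that the design forces unequal variances. It does not. Off-treatment follow-up and self-paced contact make equality doubtful, but no variance is given, and varied response to occupational therapy could make that arm the more variable one. Raising the occupational therapy variance by half, with equal correlations, gives an SE ratio of 0.96 for both robot contrasts; raising both robot arms instead gives 1.04.

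**Conclusion.** The point holds in conditional form, as a cheap improvement rather than a demonstrated error. The main analysis named in section 3.4 is valid for the arm contrasts only under an assumption that the schedule and the uneven exposure make doubtful, and nothing else in the article guards against its failure. If the pooled error is used, the usual picture with equal arms is a T2-T0 false-positive rate of about 8-10%, and a T1-T0 rate anywhere from about 3.6% to 8%, depending on how the visits correlate. A wholly transient response reverses the T2-T0 result. Arm differences in variance move the two robot contrasts apart: about 9-11% for Pepper and 4-5% for tele-robot in the case tried.

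All of these sizes rest on assumed correlations, an assumed SD ratio and an assumed 5% level, and on the contrasts taking the pooled error, which the article does not state. The recommendation does not depend on which direction the error takes.

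**What to change.** State in the analysis plan that each robot arm will be compared with occupational therapy in change at T1 and at T2 from a mixed model with an unstructured visit covariance, or with contrast-specific unequal-variance errors, using Satterthwaite or Kenward-Roger degrees of freedom. An unstructured covariance shared by all arms deals with unequal visit pairs only; let it differ by arm, or use the unequal-variance errors, to cover the Pepper arm as well. Apply the multiplicity correction to those p-values and report the confidence intervals.

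The change is one sentence. The cost is fewer error degrees of freedom for a two-arm contrast, about 48 instead of 144. The critical value rises from 1.977 to 2.011, and 2.011 / 1.977 = 1.017, so intervals would be about 2% wider if the pooled assumption did hold.
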